### Economic evaluation

An economic analysis will determine incremental cost-effectiveness for the new model of care. Health utilisation data will combine the costs of health services pre and post enrolment for each enrolled child. Average costs per activity (ED presentation, hospital admission, OP visit, GP attendance) will be applied to estimate differences in total costs. Resource use will be multiplied with unit costs to calculate the total expenditure per service area and per client before implementation of the new model of care, as well as over the study period and for each of the follow-up intervals. Relevant healthcare utilisation data will be obtained through the data linkage of the routinely collected national administrative datasets. Detailed data will be collected about care coordination, including the type and modality of care provided, duration and personnel involved in care coordination tasks and interactions with enrolled participants from primary sources. The costs to implement the RuralKidsGPS model of care will also be estimated. The study will undertake detailed probabilistic sensitivity analysis and scenario analysis to account for uncertainty within model parameters and model structure.

To estimate broader personal costs incurred by families, we will conduct a parent survey to estimate the costs associated with attending health services for their child, including accommodation, parking, meals, distances travelled (per kilometre average costs for an average vehicle); lost education opportunities (number of school days missed by the child) and missed work time based on estimates published by Mumford et. al. [7]. The cost analysis will be estimated based on the net savings of down-stream resource utilisation and funding impacts of the new model, from a health service perspective (participating health districts, as well as the state’s health system).

Outcome data will capture changes to parent and child reported quality of life assessed using the validated instruments EQ5D5L15 (parent) [8] and Paediatric Quality of Life Inventory (PedsQL4.0), and Child Health Utility 9D (CHU9D) [10] (internal consistency 𝛼 = 0.89 children and 0.92 parent report). These utilities will be included in the estimation of QALYs (quality-adjusted life-years) by calculating the area under the curve, assuming a linear change between the survey dates. QALYs calculated for the year before the intervention starts are based on the health state utility measured at baseline, which was assumed to be stable during the year before.

Cost-effectiveness will be expressed as incremental change in costs (measured by ED presentations, hospital admissions, or OP visits averted), and cost-utility by changes in QALYs gained. Cost-effectiveness will be measured between pre and post implementation of the intervention and calculated according to the formulas below:

\[\begin{array}{l}
Effect\ differences:\ \Delta QALYs = QALY{s_{post\ new\ model\ of\ care}} - QALY{s_{pre\ new\ model\ of\ care}}
\end{array}\]

\[\begin{array}{l}
Cost\ differences:\ \Delta Total\ costs = Total\ cost{s_{postnew\ model\ of\ care}} - Total\ cost{s_{pre\ new\ model\ of\ care}}
\end{array}\]

Imputation methods will be applied to missing values and sensitivity analyses will be conducted for key cost parameters in the data sets to ensure the robustness of the estimates. An additional bootstrap analysis with random 1,000-fold resampling of the original population will be conducted to ensure the validity of confidence intervals.

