## Introduction

Children and young people (CYP) who are medically complex have multiple and/or significant chronic health problems. This group represents approximately 10% of patients attending children’s hospitals, but accounts for 60% of expenditure [1,2]. CYP who are medically complex require support from different health care teams frequently based across more than one service and location. In the absence of planned coordinated care for these CYP, missed and/or duplicated care increases costs for the health system and out-of-pocket expenses for families [3]. The cost of uncoordinated care is estimated to be up to 35% higher than coordinated care [4].

A care coordination service for CYP with chronic and/or complex health conditions, developed at the Sydney Children’s Hospitals Network (SCHN) in Sydney, New South Wales (NSW), Australia, known as Kids Guided Personalised Service (KidsGPS) has already demonstrated successful outcomes in the metropolitan setting [3]. The service is focussed on CYP with increased care coordination needs due to several factors, including medical complexity, vulnerability, involvement of multiple health care teams, and reduced access to appropriate services. Evaluation of KidsGPS demonstrated a 40% reduction in emergency department (ED) presentations and 42% reduction in day-only admissions over 2 years for 534 CYP who had over 50 different diagnoses [3]. Through the adoption of KidsGPS, approximately $2.5 million/annum was saved for the tertiary hospital network, and >50,000 km of family travel was prevented [3]. Systematic review and meta-analyses data published by our research team have indicated that paediatric integrated care interventions significantly improve CYP related quality of life scores compared to usual care [5].

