*5. What is the impact of RuralKidsGPS on Parental mental wellbeing?*	Warwick-Edinburgh Mental Well-being scale [11]

*6. What is the cost of implementing the model of care? What is the cost effectiveness?*	Average costs per encounter in health service use (ED presentation, hospital admission, outpatients encounter); family cost estimates according to adapted method of Mumford et al., 2018 [7]; Quality adjusted life-years (QALYs)

*7. What are the aspects of the model of care and its implementation that support feasibility, acceptability and contextual appropriateness?*	Qualitative semi-structured interviews guided by the Consolidated Framework for Implementation Research [25]; and the Proctor Implementation Outcomes Framework [15].

*8. What are the barriers and enablers for implementing the model at scale?*	Qualitative semi-structured interviews guided by the Consolidated Framework for Implementation Research [25]; and the Proctor Implementation Outcomes Framework [15].

*9. What are the factors that will allow RuralKidsGPS to be scaled-up further?*	Survey for healthcare professionals, researchers and health care managers that includes validated tools: Short intervention acceptability, appropriateness, and feasibility measure [15], Normalization Process Theory Nomad Tool [17], Routinisation and sustainability of work practices in long term care [18].

Using NVivo qualitative data analysis software [23] we will undertake thematic analysis taking a hybrid inductive/deductive approach [24] to identify factors that help or hinder implementation, and these factors will be categorised under the CFIR constructs. Thematic analysis will specifically focus on barriers and enablers of effective behaviour change in terms of engagement with services and operation of the new model of care, whilst taking local site contextual factors into account. Such factors may include details of the setting, resource availability, staff attitudes, capabilities and capacity, and level of support from management.

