Although the KidsGPS was proven effective in the largest metropolitan children’s hospital network in Australia, its value in rural areas cannot be assumed [3]. The adaptability of the KidsGPS model to rural healthcare settings has not been evaluated, nor has this model undergone rigorous and detailed health economic evaluation to determine whether the costs of the service represent value-for-money through gains in reduced hospital utilization and shifts to lower cost settings (e.g. in primary care) where appropriate. The impacts on quality of life, for children and families, and the views of health professionals and managers implementing these models of care are poorly understood in Australia. These are important considerations for the adaptation and sustainability of such models to varied rural contexts. The mixed methods, integrated impact, implementation, and economic evaluation study outlined in our protocol will provide robust evidence of effectiveness of the model using data from four rural health settings with a geographical coverage of 420,095 km^2^. This evaluation will be the first in Australia to assess the impact, implementation, and cost effectiveness of a novel model of paediatric care coordination that could improve the health and wellbeing of children and families living in rural communities.

Successful outcomes of this research could have far-reaching healthcare policy implications for rural CYP with medical complexity. A demonstrable change in health service use and acceptability of the model by families and health care personnel, could provide strong incentive for institutionalising this model of care, providing the opportunity for children to receive quality health care in a more equitable manner, closer to home.

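### Pricing every hospital admission at one average cost biases the admission part of the cost difference whenever the mix or length of stays changes; the direction depends on which stays fall

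*Protocol article*

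**What the plan says.** The costing rule appears twice in the protocol article. In the Economic evaluation section: "Average costs per activity (ED presentation, hospital admission, OP visit, GP attendance) will be applied to estimate differences in total costs". In Table 4, question 6: "Average costs per encounter in health service use (ED presentation, hospital admission, outpatients encounter". The arithmetic is volume times price: "Resource use will be multiplied with unit costs to calculate the total expenditure per service area and per client". In both places hospital admission is a single item.

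Two other parts of the article show how much admissions can differ. The Study cohort section makes an inpatient stay of at least seven days one of three alternative service-use criteria. The Introduction summarises the metropolitan evaluation as a "40% reduction in emergency department (ED) presentations and 42% reduction in day-only admissions over 2 years for 534 CYP". It gives no figure for overnight or longer admissions.

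On uncertainty, the Economic evaluation section promises: "The study will undertake detailed probabilistic sensitivity analysis and scenario analysis to account for uncertainty within model parameters and model structure". It adds that "sensitivity analyses will be conducted for key cost parameters in the data sets to ensure the robustness of the estimates". Neither sentence names stay type or length of stay.

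**The concern.** An average price per admission gives the right saving only if the admissions averted resemble the average admission. A day-only stay and a stay of a week or more use very different resources, and a flat price treats them alike. Averted short stays are then credited at a price that long stays have raised. A programme that shortens long stays, or turns overnight care into day-only care, without changing the number of admissions is credited with nothing.

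This matters because the admission component enters the difference in total costs on which the cost-effectiveness and cost-utility results rest. The Discussion section also frames the economic question as value for money through less hospital use and a move to cheaper settings. A change in the type of stay is part of that question.

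**Working it through.** The article gives no unit cost, admission mix or projected saving for this study, so there is no planned figure to reproduce. The roughly $2.5 million a year in the Introduction is a past result of the metropolitan service, quoted without its inputs. What follows is an illustration.

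**Inputs**

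- Fall in day-only admissions, d = 0.42: from the Introduction (metropolitan service).
- Day-only share of baseline admissions, s: assumed 0.5, range 0.3 to 0.7.
- Cost of an overnight stay relative to a day-only stay, r: assumed 4, range 2 to 10. Day-only cost is set to 1.
- Fall in overnight admissions, o: assumed 0 to 50%.
- The flat price is the average at the cohort's baseline mix and is the same before and after: assumed, because the article does not say how the average is derived.

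**Formulas, per baseline admission**

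- Flat price = s + (1 − s)r
- Saving at the flat price = [d·s + o(1 − s)] × [s + (1 − s)r]
- Saving at stay-specific prices = d·s + o(1 − s)r
- Factor = flat-price saving ÷ stay-specific saving

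**Central case**, s = 0.5 and r = 4. Flat price = 0.5 + 0.5 × 4 = 2.5.

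| Overnight fall o | Flat-price saving | Stay-specific saving | Factor |
|---|---|---|---|
| 0% | 0.21 × 2.5 = 0.525 | 0.21 | 2.5 |
| 10% | 0.26 × 2.5 = 0.65 | 0.21 + 0.20 = 0.41 | 1.6 |
| 20% | 0.31 × 2.5 = 0.775 | 0.21 + 0.40 = 0.61 | 1.3 |
| 42% | 0.42 × 2.5 = 1.05 | 0.21 + 0.84 = 1.05 | 1.0 |
| 50% | 0.46 × 2.5 = 1.15 | 0.21 + 1.00 = 1.21 | 0.95 |

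If only overnight stays fall (d = 0), the factor is 0.5 × 2.5 ÷ (0.5 × 4) = 0.625, so the flat price credits 62.5% of the true saving.

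**Range over the assumed s and r**, with d = 0.42:

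- o = 0: the factor reduces to s + (1 − s)r. It runs from 0.7 + 0.3 × 2 = 1.3 to 0.3 + 0.7 × 10 = 7.3.
- o = 20%: 1.1 to 1.5.
- o = 42%: 1.0 throughout.
- o = 50%: 0.92 to 0.98.

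**Shorter stays, unchanged counts.** With s = 0.5 and r falling from 5 to 4, the true saving is 0.5 × (5 − 4) = 0.5 day-only units per baseline admission. The flat price shows 0.

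The fall in overnight admissions, relative to the day-only fall, fixes the direction of the error. The inputs s and r affect only its size.

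**The case against.** A reader might infer that the savings will be overstated because this model is known to avert day-only stays. The article does not support that. The figure comes from the metropolitan service, and silence about overnight admissions is not evidence of no effect on them. The Discussion says of the model that "its value in rural areas cannot be assumed". The Intervention section aims at avoiding unnecessary hospitalisation without restriction to short stays. Nothing shows that the sponsor expects an effect confined to day-only admissions. This part of the objection stands, and the direction must be left conditional.

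It also stands that the multiples rest on an assumed share and cost ratio, and that the largest of them require no overnight effect at all. They apply to the admission component only, not to ED, OP, GP or implementation costs.

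The next argument is that a condensed article leaves unit-cost detail to the full plan, and that an average taken separately by period or by stay type would remove the problem. That is possible. But the article does not stay silent: it states the rule twice, each time with admission as one item, and a reader would apply it as one price per admission.

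Last, scenario and cost-parameter sensitivity analyses are planned, and a stay-type scenario would fit within them. It is not named, however. Moving a single average price up or down does not tie the price to the kind of stay averted, so those analyses do not remove the error unless stay type is brought in.

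**Conclusion.** The point holds in conditional form. As written, the rule prices all admissions alike in a study where stays may run from day-only to a week or more. The admission component of the cost difference is then wrong whenever the mix or length of stays changes.

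On the central assumptions and a 42% day-only fall, the admission saving is overstated about 2.5-fold with no overnight fall and about 1.3-fold with a 20% overnight fall. It is correct with a 42% overnight fall, and slightly understated (factor 0.95) with a 50% fall. Shortened stays with unchanged counts are missed altogether.

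The share and the cost ratio are assumptions, the 42% is borrowed from another setting, and the average is assumed to reflect the cohort's baseline mix. The documents do not establish the direction for this study or the effect on total cost. This is a change worth making before analysis, not a fatal flaw.

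**What to change.** In the Economic evaluation section and in Table 4, question 6, replace the single average admission cost with one of these:

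- separate unit costs for day-only and overnight stays, the latter with a per-bed-day component; or
- the episode's casemix weight, where the linked record carries one.

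Report bed-days beside admission counts, before and after enrolment. Keep the flat average only as a sensitivity analysis, so that readers can see how much the choice matters.

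No new data collection should be needed. The comparison group is identified from linked administrative data and must meet the same service-use criteria, including the seven-day one, so length of stay has to be derivable from those data. The cost is a more detailed unit-cost table and some extra programming.

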**Figure 1 F1:**
[figure not shown]
Local Health Districts involved in the RuralKidsGPS study.

The primary aim of this evaluation is to assess the impact of RuralKidsGPS on health service utilisation (ED presentations, hospital admissions, and outpatient (OP) appointments), among CYP enrolled in RuralKidsGPS intervention compared to usual care.

The secondary aims are to:

Describe trends in health service utilisation (ED presentations, hospital admissions, OP appointments, and general practice (GP) attendances) over time;Assess the change in parent reported satisfaction with care, parental wellbeing, and parent and CYP reported quality of life at enrolment, at 6 and 12 months after recruitment to RuralKidsGPS;Assess the implementation of RuralKidsGPS model from the perspective of families, CYP, healthcare providers, managers, and practitioners, and factors that help or hinder this implementation to inform further adaption of the model and ensure scalability;Assess the cost-effectiveness of RuralKidsGPS model of care compared with standard care.

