### Study cohort

The study population includes CYP with medical complexity aged 0 to 18 years, referred for care coordination, who meet the following criteria:

– A diagnosis expected to last at least 12 months– And if ≥ 6months of age, frequent use of health services within the last six-month period, defined as:Two or more ED presentations, ORHospital admission for seven days or more, ORTwo or more outpatient appointments.

A cohort of CYP meeting these criteria and referred for care coordination, their parents and guardians, and clinical and non-clinical staff involved in the planning and/or delivery of the RuralKidsGPS model of care, will all form a part of the study cohort.

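### The economic evaluation aims at a comparison with standard care but specifies an uncontrolled pre-post contrast in children selected for recent service use, which biases gross service cost towards a fall

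*Protocol article*

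**What the plan says.** The last secondary aim, under Study design, is: "Assess the cost-effectiveness of RuralKidsGPS model of care compared with standard care".

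The Economic evaluation section fixes a different contrast. On costs: "Health utilisation data will combine the costs of health services pre and post enrolment for each enrolled child". On the measure itself: "Cost-effectiveness will be measured between pre and post implementation of the intervention and calculated according to the formulas below". The two formulas that follow give incremental QALYs and incremental total cost as the post-model value minus the pre-model value. The same pre-post basis governs the ED presentations, admissions and outpatient (OP) visits averted. Pre-year QALYs are "based on the health state utility measured at baseline, which was assumed to be stable during the year before".

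Under Study cohort, a child aged 6 months or over must show "frequent use of health services within the last six-month period": at least two ED presentations, an admission of seven days or more, or at least two OP appointments. Infants under 6 months have no use criterion.

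The Health Service Use section plans 20 frequency-matched comparison children per case from linked ED, admission and OP data, meeting the same six-month rule. Impact Evaluation Analyses uses them for the utilisation outcome. The economic section does not mention them. Patient- and family-reported measures, including those that supply utilities, are collected in the intervention cohort.

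**The concern.** There are two separate problems.

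1. **The estimator does not answer the aim.** A post-minus-pre difference in enrolled children contains no estimate of what would have happened to them under standard care over the same period.
2. **The estimator is biased by the entry rule.** A child qualifies through contacts in the six months before enrolment. Those contacts are in the pre-enrolment costs by construction, and some of them are chance excess over the child's usual rate. Use then returns towards that rate, and the pre-post formula books the return as a saving.

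The QALY formula has a related weakness. Pre-year utility is one enrolment value spread over twelve months, and no comparison child supplies a utility. Any change that would have occurred anyway is attributed to the programme.

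The Abstract promises incremental cost-effectiveness ratios, and the Discussion links the results to value for money and to making the model permanent. A ratio whose cost side leans one way under no effect could mislead that decision.

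**Working it through.** The economic section states no numerical result, so there is no figure to reproduce. The check is what the formulas return when the programme has no effect. The documents supply the entry thresholds, the post-minus-pre formulas, the flat pre-year utility, survey times of 0, 6 and 12 months, and the 3-year and 12-month windows of the impact analysis. **All rates, dispersions, cost weights and utility changes below are assumptions.**

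**Step 1: hand check, one service.** Let OP visits per half-year be Poisson with a stable child-specific rate, gamma distributed with mean 1 and frailty variance k = 1. Counts are then geometric, P(N = n) = (1/2)^(n+1). Select on N ≥ 2 in the last half-year before enrolment.
- Mean in the selecting half-year: 2 + 1 = 3.
- Mean true rate of selected children: E[(N + 1)/2 | N ≥ 2] = (3 + 1)/2 = 2. This is the mean in every other half-year, before or after.
- 12-month comparison: pre 2 + 3 = 5, post 2 + 2 = 4. The fall is 1/5 = 20%.
- 3-year comparison: pre (5 × 2 + 3)/6 = 2.167 per half-year, post 2. The fall is 0.167/2.167 = 7.7%.

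Nothing changed in these children, yet the contrast shows a reduction.

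**Step 2: simulation, three services.** ED, OP and admission counts are Poisson with a shared gamma frailty, over six half-years before and two after enrolment. Eligibility applies the Study cohort thresholds in the last pre-enrolment half-year, with 20% of admissions assumed to last seven days or more. Relative cost weights are ED 1, OP 0.4, admission 6. Frailty variance is 0.5, 1 or 2, with all or half of it stable over time. With C_t the mean cost in half-year t:
- fall against 12 months = 1 − (C7 + C8)/(C5 + C6)
- fall against 3 years = 1 − [(C7 + C8)/2]/mean(C1…C6)

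| Mean use per half-year (ED / OP / admissions) | Stable share | Cost fall vs 12 months | Cost fall vs 3 years |
|---|---|---|---|
| 0.25 / 1 / 0.15 | all | 6.9% to 13.9% | 2.4% to 4.6% |
| 0.25 / 1 / 0.15 | half | 24.9% to 29.3% | 9.4% to 11.9% |
| 0.5 / 2 / 0.3 | all | 3.2% to 5.5% | 1.1% to 1.8% |
| 0.5 / 2 / 0.3 | half | 12.7% to 19.7% | 4.7% to 7.4% |
| 1 / 4 / 0.6 | all | 1.2% to 1.5% | 0.4% to 0.5% |
| 1 / 4 / 0.6 | half | 5.3% to 12.4% | 2.0% to 4.5% |

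Cost fell in all 18 scenarios. With a further re-run, the range is about 1% to 30% against 12 months and about 0.4% to 13% against three years.

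**Step 3: sensitivity to the model.** A separate 12-month simulation with other weights, counting only long admissions, gave 6.1% to 29.6%. In that model, assuming 8 to 12 OP and 1 to 2 ED visits a year gave only 1.7% to 3.6%. Adding one shorter admission a year cut the largest fall from about 30% to 16%. Letting each service type have its own independent frailty widened the range to about 3% to 44%. The quoted ranges are illustrations, not bounds.

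**Step 4: controlled contrast.** Under the Step 2 model, comparison children selected by the same rule over the same window show the same expected fall. The difference-in-differences then has expectation 0.

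**Step 5: QALYs.** If utility rises naturally by d by month 6 and stays level, area under the curve minus the flat pre-year is 0.5 × (d/2) + 0.5 × d = 0.75d. For d = 0.02, 0.05 and 0.10 the formula credits 0.015, 0.0375 and 0.075 QALY per child. A natural decline gives the same amounts with a negative sign.

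**The case against.** The strongest points on the other side:

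- **Pre-enrolment care is a historical form of standard care.** That is a fair description, but it removes neither regression to the mean nor time trends.
- **The article condenses a fuller plan.** This does not help, because the article prints the estimator as formulas and they contradict its own aim.
- **Uncertainty is handled.** Probabilistic sensitivity analysis, scenario analysis, imputation and the 1,000-fold bootstrap deal with parameter, structural, missing-data and sampling uncertainty. None is said to supply a comparator. The interrupted time series is not tied to the economic analysis.
- **Net savings do not follow.** A reader might infer that the plan would report savings under no effect. The documents do not support that. Coordination activity and implementation costs are also to be estimated and could outweigh a spurious fall. Infants under 6 months have no use criterion and a truncated pre-period, which may push the other way. This objection stands, and the claim is limited to gross service cost.
- **The cost window is not stated.** The year before enrolment is named for QALYs only, and the one utilisation baseline given is three years, which shrinks the artefact. This also stands, so both windows are shown.
- **Direction of the QALY bias.** A reader might infer that enrolment is a low point in quality of life, or that ageing lowers cost. Nothing in the documents shows either. Entry is on service use, which two OP visits can satisfy, and on a diagnosis expected to last at least 12 months.
- **It is the last-listed secondary aim.** The utilisation outcome has its matched comparator and is not affected by this point.

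**Conclusion.** The concern holds in a limited form. The text establishes the mismatch between aim and estimator without any assumption. The expected downward bias in gross service cost follows from the entry rule whenever use varies over time within a child. Its size cannot be fixed from the documents: it may be trivial where usual use is well above the thresholds and the pre-period is long, or of the same order as the 20% difference in use on which the study is powered. The sign of the net cost difference is not determined. For QALYs, what is shown is an untested stability assumption with no control, not a bias of known direction. Because ratios are promised in the Abstract and a decision on the model's future is in view, this should be corrected before the economic analysis is run.

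**What to change.** - Define incremental cost, and ED presentations, admissions and OP visits averted, as (post minus pre) in RuralKidsGPS children minus (post minus pre) in the matched comparison children.
- State the windows. Use equal lengths or annualised rates, which also deals with truncated infant pre-periods, around an index date at which both groups meet the six-month use rule.
- Include coordination and implementation costs, already planned for estimation, in the intervention arm.
- Bootstrap within the frequency-matching strata, since no individually matched sets are described.
- Label cost per QALY as an uncontrolled pre-post scenario and do not present it as a comparison with standard care.

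The cost is some extra analysis of linked data already planned, plus wording. The QALY result drops to a scenario, and GP costs may be available for enrolled children only. Some bias can remain, because cases were referred for coordination while comparison children need only meet the use rule. The report should say so.
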